#### Non-adherence, retention, and withdrawal

Participants in the intervention phase who reject ACP are a vital part of the analysis since the *offer* of ACP is the intervention. Therefore, they remain part of the intervention group, and their decision to reject ACP will be recorded. The same applies to participants in the intervention phase who initially accept ACP but fail to attend all or part of the ACP appointments. Both groups are asked to fill in a short questionnaire on the reasons for rejection or cancellation (see section “Instruments”).

Of course, any participants may withdraw from the study at any time without giving reasons. Nonetheless, in order to avoid bias from selective withdrawal, we seek to increase retention by designing the study follow-up as a low-threshold telephone interview integrated into routine care, so participants will not need to be at the clinic for it and still have a benefit from the possibility to ask questions concerning their diagnosis and therapy.

### Instruments

All questionnaires are available to the interested reader on request. A decision flow chart for questionnaire presentation can be found in “Appendix A”.

#### Primary outcome advance directive: existence and validity

Information on the existence and validity of the advance directive is collected at T0 in a self-report questionnaire and at T2 in a telephone interview. The closed questions were specifically composed for this study.

First, the existence of an advance directive is recorded (“Do you have an advance directive? Yes/no). This question acts as a filter: If no advance directive is available, none of the subsequent questions follows. If the answer is yes, the validity of the advance directive is assessed.

Since advance directives are highly-sensitive personal data, determining their validity via their content is ethically problematic in our view. One approach, therefore, is to ask whether informed consent was given by the participant when the declaration was drawn up, meaning (1) a patient capable of giving consent, (2) had received adequate information to make an informed decision, and (3) this decision had been voluntary [10]. The respective questions with dichotomous response options (yes/no, supplemented by “don’t know”), can be found in Table 2.

**Table 2 Tab2:** Questions on the validity of the advance directive

	Question
Prerequisite	Has the advance directive been made with a notary, physician or psychotherapist?
Adequate information	Has there been a medical/psychotherapeutic consultation?
	Has there been a notarial consultation?
Capacity to consent	Has your capacity to consent been documented by the physician/psychotherapist or the notary when the advance directive was drawn up?
Voluntariness	Did you create the advance directive voluntarily?

Besides asking about participants’ advance directive, in this questionnaire, we also ask about the existence of a guardianship, a guardianship directive, or a lasting power of attorney.

#### Secondary outcome advance directive: satisfaction

Satisfaction with the (latest) advance directive is assessed at T0 and T2.

In order to minimize time expenditure, a single item with a five-point response scale is used to record satisfaction with the respective advance directive ("How much do you agree to the following sentence: I am satisfied with my advance directive.—Does not apply at all—Applies very much"; also see Lattuca et al., 2018), supplemented by a “don’t know” option.

#### Rejection of ACP

For participants in the intervention group who decline the ACP offer, a closed-ended question will ask about reasons for refusal. The response alternatives are presented in Table 3.

**Table 3 Tab3:** Reasons for rejecting ACP

*Please circle the answer that applies to you. Multiple answers are possible* *I don’t want to take part in ACP because…*	
• I don’t want to create my advance directive • I already have an advance directive that I am satisfied with • The whole process is physically/mentally too demanding for me • The whole process is emotionally too demanding for me • I prefer to make my advance directive later • I cannot make the additional appointments • Others (please name the reasons)	

#### Potential predictors of the existence of valid advance directives

In addition to demographic data (age, gender, education), the need for autonomy in medical decision making, health literacy, somatic and psychiatric comorbidities, as well as the severity of dementia are assessed.

Demographic data are collected at T1 and T2.

The need for autonomy in medical decisions will be assessed at T1 using a single item by [11], translated to German and adapted for the needs of this study. The item asks who should decide about a medical treatment; the answers range from *no need for autonomy* (decision is made solely by the physician) to a *very high need for autonomy* (decision is made solely by the patient) on a five-point scale.

Health literacy will also be assessed at T1 using a single item by [12], translated for this study. Participants are asked to rate, on a five-point scale, how much difficulty they have with reading medical information.

Comorbidities will be recorded at T1 with the help of the CIRS-G (Cumulative Illness Rating Scale-Geriatric) [13]. Using this questionnaire, the treating physician rates the severity of the damage to 13 body systems, functions, and organs, as well as the severity of psychiatric impairment. Severity ratings range from *no damage* to *severe damage* on a five-point scale. For the somatic damage, a sum score of the 13 single body damage ratings is calculated with the somatic morbidity index (SMI). The psychiatric impairment score is used as a single item.

In addition, the German version of the 15-item short form of the GDS [9] is used. It is a renowned screening instrument for depression in geriatric settings, which considers the differing symptoms depression may present in older age.

Finally, the MMSE, a well-known screening instrument is used at T1 and T2 to assess the degree of patients’ cognitive dysfunction. In this study, we use the MMSE version contained in the CERAD-Plus (neuropsychological test battery for dementia by the Memory Clinic Basel, see, e.g. [14]). It is routinely assessed by the treating neuropsychologist^4^ during the neuropsychological assessment at T1 and transferred to the T2 documentation. At T2, when the final diagnosis has been made, the severity of dementia is recorded by a single item reflecting the diagnosis communicated to the patient (no dementia—mild cognitive impairment—mild dementia—mild to moderate dementia—moderate dementia—severe dementia^5^—not yet diagnosed).

### Statistical evaluation

#### Statistical methods of evaluation

The first two research questions of study part 1 (about the presence and validity of advance directives and the patients’ satisfaction with them) are merely descriptive. For research question 3 (about the association between patient-related characteristics and the presence of a (valid) advance directive), a logistic regression model is fitted with and without consideration of the validity of the advance directive, respectively. Factors entered into the model are demographic variables, need for autonomy in medical decision-making, health literacy, comorbidity, and the severity of dementia as assessed by MMSE. All data used in these analyses are gathered at T1.

In study part 2 (intervention), question 4 (the hypotheses that the proportions of patients with either only a valid advance directive or with an advance directive, regardless of its validity, are higher after the offer of ACP than during the baseline phase), will be tested using a chi-squared test for comparison of two independent samples. To allow for cases of incomplete ACP at the time of assessment (T2), a sensitivity analysis that considers the potential of valid advance directives will be conducted.

Confirmatory testing is only planned for the first hypothesis in question 4 (that the weekly proportions of patients with a *valid* advance directive are higher during the intervention phase). So alpha error adjustment for multiplicity is not necessary.

For question 5 (the association between ACP and satisfaction with advance directive), an asymptotic Wilcoxon-Mann–Whitney test for comparison of two independent samples will be used.

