## Methods

### Settings and participants

Participants will be recruited from two outpatient memory clinics (University Hospital Frankfurt, Germany; Kreisklinikum Siegen, Germany). We plan to recruit at least *n* = 125 participants at each location, with a total of *N* = 250 participants. This will be a convenience sample: Each patient presenting in either of the two clinics during the data assessment period (25 weeks for baseline and intervention phase, respectively) will be asked for participation as long as the inclusion criteria are fulfilled.

Patients are eligible for participation in the study if they present with suspected (mild or moderate) dementia. Since the capacity to consent to study participation could be an issue, the inclusion process will be based on the decision tree for the inclusion of non-consenting individuals in medical research [8]. Also, this allows us to include participants with questionable capacity to consent.

Exclusion criteria for study part 1 (status quo) are lack of capacity to consent to medical research with simultaneous incapacity for supported decision making by a relative or proxy or the lack of participant’s assent.

Exclusion criteria for study part 2 (intervention: ACP offer) are a final diagnosis of severe dementia by clinical rating, delirium, intellectual disability, severe mental illness, lack of capacity to consent to medical research with simultaneous incapacity for supported decision making by a relative or proxy, no assent by the patient, uncompensated pronounced sensory deficits, or insufficient knowledge of the German language, which makes the understanding of the study documents and/or the interview impossible.

In both study parts, there are no restrictions regarding concomitant interventions. Simulations were performed to determine the power of the analysis for our principal hypothesis: The proportion of valid advance directives increases when patients are offered ACP. Assuming that the proportion of valid advance directives during the baseline phase is 25% and can increase to 50% by offering of ACP and that an average of five patients are included weekly, the power is approximately 95%. We are positive to reach this number of participants; nonetheless, the sample size is constrained by the capabilities of the two participating outpatient memory clinics.

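### Clinic is missing from the research question 3 models and from the confirmatory test; where the two clinics differ, this can distort the predictor odds ratios and, if the clinic mix also shifts between phases, the phase comparison

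*Protocol article*

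**What the plan says.** Under Settings and participants: "Participants will be recruited from two outpatient memory clinics", a university hospital in Frankfurt and a district hospital in Siegen. The target is at least "125 participants at each location, with a total of" 250. That target covers both phases together, and no number per clinic within a phase is given. Recruitment is by convenience ("Each patient presenting in either of the two clinics during the data assessment period" is asked to take part if eligible), and "the sample size is constrained by the capabilities of the two participating outpatient memory clinics".

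Under Statistical methods of evaluation, the research question 3 logistic models are specified by a list: "Factors entered into the model are demographic variables, need for autonomy in medical decision-making, health literacy, comorbidity, and the severity of dementia", the last measured by MMSE. The section on potential predictors gives the demographic data as age, gender and education. The hypotheses on the proportion with a directive (valid, or of any kind) "will be tested using a chi-squared test for comparison of two independent samples". The only sensitivity analysis named for that comparison concerns ACP that is incomplete at T2. Clinic is not a covariate, a stratum or a sensitivity factor anywhere in the article.

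**The concern.** Clinic is an obvious candidate for a common cause of predictors and outcome in a two-centre study. Validity is scored from items on consultation with a physician, psychotherapist or notary and on documented capacity to consent, and local practice may vary on these. The comorbidity predictor (CIRS-G) is rated by the treating physician, so any difference between raters coincides with clinic. If a predictor and the directive rate both differ by clinic, a model without clinic credits part of the clinic difference to the predictor. The Discussion intends these associations to identify groups for targeted intervention.

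In part 2 the phases follow one another in time and each clinic's share of enrolment is left to capacity. If the clinics have different directive rates and their shares change between phases, the pooled proportions differ even when the offer does nothing.

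**Working it through.** **Inputs from the protocol.** Two clinics; at least 125 participants each, 250 in total; 25 weeks per phase at a mean of five patients per week, so about 125 per phase; valid directives 25% at baseline and 50% with the offer.

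**Assumptions, not in the protocol.** Two-sided alpha of 0.05; clinic rates set symmetrically around 25% (a 20-point gap means 35% and 15%); the predictor difference between clinics; the shift in clinic mix.

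**The plan's own figure.** The protocol says that with "an average of five patients are included weekly, the power is approximately 95"%. For the named chi-squared test with 125 per phase:

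power = Φ[(0.25 − 1.96·√(2·0.375·0.625/125)) / √((0.25·0.75 + 0.50·0.50)/125)] = Φ[(0.25 − 0.120)/0.0592] = Φ(2.20) = 98.6%.

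A figure near 95% appears if weekly proportions are simulated with Poisson(5) patients per week (Mann-Whitney 95.3%, t-test 94.5%). Either way, power is not what this point turns on.

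**Research question 3.** Simulation with 125 patients per clinic, a 25% overall rate, one normally distributed predictor with no effect within clinic, and 3,000 runs:

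| Rate gap (points) | Predictor difference (SD) | OR per SD, no clinic term | False positives, no clinic term | False positives, clinic term |
|---|---|---|---|---|
| 10 | 0.5 | 1.07 | 7.1% | 5.1% |
| 20 | 0 | 1.00 | 5.1% | 5.5% |
| 20 | 0.25 | 1.07 | 8.1% | 5.2% |
| 20 | 0.5 | 1.13 | 13.4% | 4.7% |
| 30 | 0.5 | 1.22 | 27.2% | 4.9% |
| 30 | 0.75 | 1.32 | 50.4% | 4.7% |

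With a clinic term the odds ratio is about 1.00 throughout. Where the predictor does not differ between clinics there is no bias.

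**Phase comparison, no effect of the offer.** Expected spurious difference = (rate gap) × (shift in the higher-rate clinic's share). For a 20-point gap and a share moving from 40% to 60%:

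- Baseline: 0.40·35% + 0.60·15% = 23%. Intervention: 0.60·35% + 0.40·15% = 27%. Difference: 4 points.
- The test rejects beyond 1.96·√(2·0.25·0.75/125) = 10.7 points.
- The standard error of the difference with fixed clinic numbers is √[(125·0.35·0.65 + 125·0.15·0.85)/125²] = 5.33 points.
- Upper tail: 1 − Φ((10.7 − 4)/5.33) ≈ 10.3%. Lower tail ≈ 0.3%. Total: between 10% and 11%.

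Simulation (100,000 runs) agrees:

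| Rate gap (points) | Share of higher-rate clinic, baseline to intervention | Spurious difference (points) | Pooled chi-squared, two-sided | Stratified (Cochran-Mantel-Haenszel) |
|---|---|---|---|---|
| 10 | 40% to 60% | 2 | 6.4% | 5.1% |
| 20 | 50% to 50% | 0 | 4.3% | 4.9% |
| 20 | 40% to 60% | 4 | 10.4% | 5.0% |
| 30 | 40% to 60% | 6 | 17.9% | 5.0% |
| 20 | 30% to 70% | 8 | 30.6% | 5.1% |

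A milder 45%-to-55% shift at a 20-point gap gives 6.0%. If the mix varies only by chance around equal shares, simulated rejection is 4.9%.

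**The case against.** Nothing in the protocol says that the clinics differ in education, health literacy, comorbidity ratings or directive rates. A reader might infer that clinic differences will be reported as patient-level predictors. The documents support only that this can happen where the clinics differ on both sides of the association.

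A reader might also infer that the confirmatory test is invalid as planned. It is not. Both clinics run both phases, so clinic is not built into the contrast. The Discussion expects at least five patients a week in each clinic and offers the sites extra staff; that is no quota, but it points to a steady flow from both. A 40%-to-60% shift is about 3.2 standard deviations of chance variation (0.20/√(2·0.25/125) = 0.20/0.063), so it needs a systematic cause that the protocol does not describe. The spurious 4 points also compare with a planned difference of 25.

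For research question 3, larger figures can be produced. With higher education in 70% of one clinic's patients and 35% of the other's, and valid directives at 35% and 15%, the crude odds ratio is 1.46 (28.3% against 21.3%) with no association inside either clinic. That is a single-variable 2×2 figure and should not be read as what the planned multivariable model would give. The simulation above also uses one predictor, so it shows the mechanism and its rough size only. Part 1 is exploratory, and an association across the pooled population is a legitimate description; it just should not be taken for an association that holds within a clinic.

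Finally, a fuller plan may add clinic. But the article does not leave the matter open: it lists the factors and names the test. These objections limit the size of the problem and make the phase comparison the weaker part. They do not remove the omission.

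**Conclusion.** The point holds in conditional form. The published factor list and the published test both ignore clinic, in a study that pools two centres without fixing their shares per phase.

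- **Research question 3:** distorted only if the clinics differ in both a predictor and the directive rate. At an assumed 20-point gap and 0.5 SD, a null predictor shows an odds ratio of about 1.13 per SD and about 13% false positives instead of about 5%.
- **Phase comparison:** distorted only if the rates differ and the mix shifts systematically. At 20 points and 40% to 60%, the two-sided error is about 10% instead of 5%. With a stable mix the pooled test is slightly conservative.

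The clinic gaps, shifts and alpha are assumptions. The change is worth making because it is cheap, not because the primary result is shown to be at risk. It does nothing about calendar-time confounding between the sequential phases, which is a separate matter.

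**What to change.** 1. Add clinic as a fixed effect to both research question 3 logistic models (any directive, valid directive).
2. Analyse the confirmatory comparison with a Cochran-Mantel-Haenszel test stratified by clinic. If the chi-squared test stays primary, pre-specify the stratified test as a sensitivity analysis.
3. Report the part 1 prevalences and the part 2 risk difference per clinic as well as combined. A stratified test alone would not show an effect confined to one clinic; only per-clinic results do.
4. Confirm that the database keeps a clinic code. The per-clinic target and the storage of records at each site make this likely, but no section lists clinic as a variable, and the data are described as anonymised at source with the paper records later destroyed.

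**Cost.** One degree of freedom per logistic model, a change of wording in the analysis section and, if the clinic code exists, no new data. Power is essentially unchanged with 125 per phase and an even mix (pooled against stratified): 98.6% and 98.6% with no clinic gap, 98.8% and 98.9% with a 20-point gap, 99.0% and 99.2% with a 30-point gap.

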### Study aims, research questions & hypotheses

The study’s aims include (a) to investigate the proportion of valid advance directives in a memory clinic population of suspected PwAD, (b) to determine the predictors of valid advance directives, and (c) to examine whether the offer of ACP can increase the proportion of valid advance directives in PwAD.

This study consists of two parts:

In part 1, we assess the status quo of advance directives in memory clinics. Part 1 is descriptive and explorative and uses an observational single-group design to answer the following research questions:What is the proportion of patients with (valid) advance directives in the population of memory clinic patients?How satisfied are memory clinic patients with their advance directives?Do demographic variables (age, gender, education, health literacy, need for autonomy, comorbidities, and/or dementia status) predict the existence and validity of advance directives?Study part 2 investigates the effects of offering ACP to memory clinic patients and is conceived as a non-randomized comparative trial with a baseline and an intervention phase. It is assumed that the offer of ACP is superior to no intervention (“care as usual”). The following hypotheses are investigated:When offered to take part in ACP (the intervention phase of the study), the proportion of patients with (valid) advance directives will be significantly higher than in the preceding baseline phase without the offer of ACP.When offered to take part in ACP (intervention phase of the study), the satisfaction of patients with their advance directives will be significantly higher than in the preceding baseline phase without the offer of ACP.

This study is a part of the comprehensive research project DECIDE (*Deci*sion-making places in Alzheimer’s *de*mentia—supporting advance decision-making by improving person-environment fit). DECIDE aims to enable PwAD benefit from their right to self-determination as much as possible.

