### Study design, intervention, and outcomes

In study part 1 (status quo), the overall sample is used in an observational cross-sectional single-group design. Outcomes are (1) the presence of an advance directive and its validity, (2) the patients’ satisfaction with this advance directive regardless of its validity, all assessed when patients present at the memory clinic for the first time.

In addition to this descriptive part, potential predictors of the presence of a (valid) advance directive are investigated. Variables of interest are demographic variables (e.g., age, gender, education), health literacy, need for autonomy in medical decision-making, cognitive status measured by the Mini-Mental State Examination (MMSE), mental health determined by the Geriatric Depression Scale (GDS), and physical and mental health status measured by the Somatic Morbidity Index (SMI) or the mental health score, respectively, of the Cumulative Illness Rating Scale—Geriatric (CIRS-G).

Study part 2 (intervention) uses a two-sample design with a blockwise allocation to baseline and intervention group. Hence, there is a baseline phase of 25 weeks, during which none of the participants receives ACP, and an intervention phase of 25 weeks, during which every participant receives ACP.

The intervention is the *offer* of an ACP (no: baseline phase/yes: intervention phase), but not the ACP process itself. The offer is made by the treating physician at the memory clinic, who also performs the informed consent procedure and collects the data.

The outcomes in this study part are the same as in study part 1: (1) the presence of an advance directive and its validity, and (2) the patients’ satisfaction with the existing advance directive (valid or not); always referring to the participant’s latest advance directive.

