### Procedure

#### Data collection

The procedure is presented in Fig. 1. Data for study part 1 (status quo) is assessed at T0 and T1, data for study part 2 is assessed at T2.

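### The only confirmatory test is an unadjusted chi-squared on T2 status between two non-randomised phases, so a systematic phase difference in pre-existing valid directives passes largely into the estimated effect of the ACP offer

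*Protocol article*

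**What the plan says.** The aims section says that part 2 "is conceived as a non-randomized comparative trial with a baseline and an intervention phase". The design section calls it a "two-sample design with a blockwise allocation to baseline and intervention group", each phase lasting 25 weeks at the same two clinics. The data collection section states that "data for study part 2 is assessed at T2".

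The statistical methods section says the question 4 hypotheses "will be tested using a chi-squared test for comparison of two independent samples", and adds: "Confirmatory testing is only planned for the first hypothesis in question 4", namely the one on valid directives. The one sensitivity analysis named for that question deals with ACP still unfinished at T2.

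The same outcome is also measured before any offer. Existence and validity of the directive "is collected at T0 in a self-report questionnaire and at T2 in a telephone interview". Part 1 uses this for the whole sample, hence for both phases. Age, education, health literacy, comorbidity and MMSE enter only the part 1 regression.

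Two further statements bear on the point. The outcome always refers to the latest directive (study design section), and a participant whose ACP is unfinished at T2 answers about any directive already held (procedure section). T2 therefore includes pre-existing directives. Nothing in the article adjusts the part 2 comparison or checks that the phases are comparable, and the pitfalls in the Discussion do not raise it.

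**The concern.** In a randomised trial an unadjusted chi-squared is valid and only loses some precision. Here allocation is by calendar period, so nothing in the design balances the phases. Referral patterns, season, the share contributed by each clinic, or willingness to consent could all shift the proportion who arrive with a valid directive. Such people mostly still have one at T2, so the shift appears in the T2 comparison and is read as an effect of the offer.

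The error can go either way: a higher starting level in the intervention phase can produce a false positive, and a lower one can hide a real benefit. This test carries the trial's only confirmatory claim, and the variable that would absorb most of such a shift is already planned for collection.

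**Working it through.** **The plan's own figure.** The article assumes 25% versus 50% valid directives and an average of five patients per week, giving 125 per phase and 250 in all, with power of about 95%. Alpha is not stated; I take two-sided 0.05. For the planned chi-squared, power = Φ((Δ − 1.96·SE0)/SE1).

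- Pooled proportion 0.375: SE0 = √(2 × 0.375 × 0.625/125) = 0.0612.
- SE1 = √((0.25 × 0.75 + 0.50 × 0.50)/125) = 0.0592.
- Power = Φ((0.25 − 0.1200)/0.0592) = Φ(2.20) = 98.6%.

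This is above the stated 95%. A simulation on weekly proportions (Poisson accrual, Wilcoxon-Mann-Whitney test) gives 95.5%, so the stated figure may come from a different analysis. That does not affect the present point.

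**Assumed model, not from the article.** T0 validity is 25% in the baseline phase. Of directives valid at T0, 95% are valid at T2. Of participants without one, 2% acquire one without an offer. Then

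P(valid at T2) = 0.95·p + 0.02·(1 − p) = 0.02 + 0.93·p,

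so 93% of any T0 difference passes into the T2 difference. A 10-point imbalance gives 9.3 points of apparent effect.

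**Hand check at 10 points, no effect.** T2 proportions are 0.2525 and 0.3455, a difference of 0.093. The pooled proportion is 0.299, SE0 = 0.0579, SE1 = 0.0576. Rejection = Φ((0.093 − 0.1135)/0.0576) = Φ(−0.36) = 36%.

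**Simulation, no effect of the offer, 125 per phase** (stratified means Cochran-Mantel-Haenszel by T0 status):

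| Assumed T0 imbalance | Crude chi-squared | Stratified, T0 error-free | Stratified, T0 sens. 80%, spec. 95% | Stratified, T0 sens. 70%, spec. 90% |
|---|---|---|---|---|
| 5 points | 13% | about 5% | 8% | 10% |
| 10 points | 36% | about 5% | 16% | 23% |
| 15 points | 66% | about 5% | 29% | 44% |

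With no systematic imbalance both tests reject in about 5%.

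**Sensitivity to the persistence assumption.** If every valid directive persists and 5% of the others acquire one in either phase, the crude rates are 12%, 36% and 66%. If T2 status equals T0 status exactly, they are 14%, 41% and 73%.

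**Opposite direction.** Take T0 validity 35% in the baseline phase and 25% in the intervention phase, with full persistence, and let the offer raise new valid directives from 5% to 20% of those without one. The crude test then favours the offer in 4.5% of trials, the T0-stratified test (error-free T0) in 87%.

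**Precision without imbalance, error-free T0.** At roughly the planned effect, the SD of the risk difference falls from 5.9 to 4.2 points, a variance ratio of (4.2/5.9)² = 0.51. Crude power there is already about 98%. For a 12-point effect, power rises from about 54% to 95%; with T0 sensitivity 80% and specificity 95% it reaches about 75%.

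**Calendar week.** Over 50 weeks, week number and phase correlate at 0.87. Variance inflation is 1/(1 − 0.75) = 4, so the SE of the phase effect doubles.

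**The case against.** The strongest reply is that the harm is conditional and its size is not in the documents. That stands: the article gives no between-phase figure, and the imbalances, persistence and conversion rates above are assumptions. Some design features limit drift. Every eligible patient who presents is asked, the same two clinics serve both phases, and baseline participants are also to be offered ACP outside the study within six months, which narrows any difference in incentive to consent. These features reduce selection but do not exclude it.

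A reader might go further than the documents allow in four ways.

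- Chance imbalance in T0 status (SE about 5.5 points) might be counted as bias. It is not: it lies within the chi-squared's nominal size and costs only precision.
- T0 adjustment might be thought to cure the problem. T0 is self-report by people with suspected dementia, with a don't-know option and possible proxy answers, so correction is partial. It also leaves secular trends in new directives and unmeasured readiness to make one.
- The trial might be thought underpowered without adjustment. At its planned effect it is not; the gain matters only if the true effect is smaller.
- T2 status might be taken as simply T0 status because follow-up is short. The three to four weeks run from the last appointment; the time from T0 across the three appointments is not given.

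It may also be said that baseline tables and adjusted supportive analyses belong in an analysis plan not shown. That is fair, and their absence is not the criticism. The article itself fixes the confirmatory test, and that choice can be judged as it stands.

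**Conclusion.** The point holds as a flaw in the choice of confirmatory test. In this non-randomised comparison, a systematic phase difference in T0 valid-directive status goes largely into the estimated effect: about 93% under the assumptions used, not necessarily one for one. If such differences were 5, 10 or 15 points, the crude test would reject a null effect in about 13%, 36% or 66% of trials. Whether the phases will differ at all is unknown, so these rates show vulnerability and are not a forecast.

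Stratifying by T0 status lowers the false rejection rate to between about 5% (error-free T0) and 8%, 16% and 29% (80% sensitivity, 95% specificity), and higher still if T0 is measured less well. It makes the result more credible but does not turn the design into a randomised one. The variance roughly halves at the planned effect if T0 is error-free, which is a secondary benefit.

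**What to change.** 1. Name one confirmatory test: a Cochran-Mantel-Haenszel test of T2 valid-directive status by phase, stratified by T0 valid-directive status and clinic. Fix beforehand a T0 category for don't-know answers. Report a risk difference standardised over the strata, with a 95% CI.
2. Keep the crude chi-squared as supportive, and add one supportive logistic model with phase, T0 status, clinic, age and MMSE.
3. Report the proportion with a valid directive at T0 by phase. T0 precedes any offer in both phases, so this shows directly whether they started alike.
4. Treat a calendar-week model as optional. With week and phase correlated at 0.87 it will be imprecise.
5. State in the limitations that adjustment does not deal with secular trends or unmeasured readiness.

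The cost is mainly wording; no patients, visits or variables are added. One practical point could cost more. The confidentiality section says the data are made anonymous where they are collected, and the adjusted test needs each participant's T0 and T2 records to be joined. The sponsor should confirm that a pseudonymous code does this. Carrying the T1 MMSE into the T2 documentation suggests some linkage exists, but the article does not say so. If there is none, data collection must change, and the registry appendix lists the trial as already recruiting.
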